### End of trial

Recruitment will cease when the last patient is randomised following our sample size recommendation. The end of the trial is expected when the last 6-month follow-up data is collected.

### Sample size

Target sample size: 220 (110 in each intervention and control group).

### Rationale

According to the data presented by Allingstrup et al. [9] we estimated that 200 patients are needed to show a 15% relative reduction in the primary outcome (physical component of SF-36 score at 6 months) corresponding to a difference of 5.5 points (minimal clinical important difference defined as half a standard deviation from the observed dataset in the presented study) between the intervention and the control group at a significance level of 0.05 and a power of 80%. The calculations were based on a PCS of 37.5 (SD 10.65) among survivors from their data. The PCS SF-36 did not differ between the intervention and control groups at 6 months in the general ICU population in this study. Moreover, we increased the number of patients in our study to 220 assuming a 10% loss to follow-up among survivors from ICU. We hypothesised that early SPN might influence the long-term outcome of critically ill patients after oncological surgery of the gastrointestinal tract that constituted only 6% of the intervention group and 12% of the control group of the study mentioned above.

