### Hypothesis

We hypothesise that early goal-directed supplementation of proteins in SPN may significantly increase the number of points in the physical component score (PCS) at 3 and 6 months after admission to ICU in the population of critically ill patients after oncological surgery of the gastrointestinal tract.

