### Missing data

We assumed a 10% loss to follow-up among the population that completed the trial and enlarged the sample size from 200 to 220 participants.

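### The stated inputs call for about 120 patients, not 200, so the sample-size statement misreports its basis or its power; the mismatch makes the trial larger than needed, not underpowered

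*Protocol article*

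**What the plan says.** The Rationale under Sample size in the protocol article sets out a full calculation. It says "we estimated that 200 patients are needed to show a 15% relative reduction in the primary outcome", "corresponding to a difference of 5.5 points" on the PCS at 6 months, "at a significance level of 0.05 and a power of 80" per cent. It explains the 5.5 points as a "minimal clinical important difference defined as half a standard deviation" and adds: "The calculations were based on a PCS of 37.5 (SD 10.65) among survivors from their data". Allocation is 1:1 (Randomisation).

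The 200 is then raised to 220, 110 per arm, for a 10% loss to follow-up that the Rationale applies to survivors from the ICU. The Missing data section repeats that the authors "enlarged the sample size from 200 to 220 participants". Neither place gives a mortality rate or a separate allowance for death. The Statistical analysis section names Wilcoxon's test and linear regression for the PCS and expects non-normal data. The article does not say whether the significance level is one-sided or two-sided.

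**The concern.** Difference, SD, alpha, power and allocation are all printed, so the number can be checked directly. Half an SD at 80% power is a familiar case that needs a little over 60 per arm, and 100 per arm is far above that. Either a printed input is not the one used, or an allowance was added and not mentioned.

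The statement governs how a neutral result is read. As printed, a reader assumes a 20% chance of missing a true 5.5-point effect. If the printed inputs are right and 200 patients are evaluable, that chance is about 5%. If a larger SD was the real basis, 20% may be right but the printed SD is wrong. The text does not let the reader tell these apart.

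A second gap adds to this. The SD and the loss rate both refer to survivors, while 200 and 220 are numbers of patients to be recruited. Without a mortality assumption, the expected number with a 6-month PCS cannot be worked out.

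**Working it through.** **Inputs.** From the Rationale: difference 5.5, SD 10.65, alpha 0.05, power 80%, mean 37.5, loss 10%. From Randomisation: 1:1. Assumed here: a two-sided test.

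**Step 1: try to reproduce 200.** Normal approximation, per arm:

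n = 2 × (1.960 + 0.842)² × SD² / difference² = 2 × 7.849 × 10.65² / 5.5² = 58.9.

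With the noncentral t distribution n = 59.8, so 60 per arm and 120 in total. The figure of 200 is not reproduced; it is 200/120 = 1.67 times the requirement.

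**Step 2: variants at alpha 0.05 and 80% power** (t-based totals).

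| Variant | Total |
|---|---|
| As printed, two-sided | 120 |
| As printed, one-sided | 96 |
| Difference 5.325 (half of 10.65) | 128 |
| Difference 5.625 (15% of 37.5) | 116 |
| 5.5 points, Wilcoxon efficiency 0.955 | 126 |
| 5.5 points, Wilcoxon worst-case efficiency 0.864 | 140 |
| 5.325 points, SD 11, efficiency 0.864 | 158 |

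The last row is the largest variant tried. None reaches 200.

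**Step 3: what would give 200.** Change one input and keep the rest, with 100 per arm:

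- SD of about 13.8 instead of 10.65 (t-based).
- Difference of about 4.24 instead of 5.5, that is 4.24/10.65 = 0.40 SD.
- Power of 95% instead of 80%, which needs 98.4, so 99 per arm and 198 in total.

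**Step 4: power at the printed inputs.** With 200 evaluable it is 95.3% (t-test); with 198 it is 95.1%.

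**Step 5: loss and death.** The 10% was applied as 200 × 1.10 = 220. In reverse, 220 × 0.90 = 198, whereas 200/0.90 = 222.2, so 223. For mortality m by 6 months, evaluable = 220 × (1 − m) × 0.90. The mortality values are assumptions, as the article gives none, and the table supposes that patients who die have no PCS.

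| Assumed mortality | Evaluable | t-test power, 5.5 points | Wilcoxon (efficiency 0.955) |
|---|---|---|---|
| 0% | 198 | 95% | 94% |
| 10% | 178 | 93% | 92% |
| 20% | 158 | 90% | 88% |
| 30% | 139 | 86% | 84% |
| 40% | 119 | 80% | 78% |

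The 120 needed for the t-test are retained while 198 × (1 − m) is at least 120, so up to m = 1 − 120/198 = 39%. For 126 (Wilcoxon, 0.955) the limit is 1 − 126/198 = 36%; for 140 (worst-case efficiency) it is 29%.

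**Step 6: wording of the target.** Half of 10.65 is 5.325, 15% of 37.5 is 5.625, and 5.5/37.5 = 14.7%. The Rationale speaks of a reduction, whereas the Hypothesis section expects early supplementation "may significantly increase the number of points in the physical component score (PCS").

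**The case against.** The best defence is that the discrepancy is in the safe direction. On its own inputs the trial is larger than it needs to be, and the surplus may be a deliberate but unstated margin for deaths or for a wider spread in this population. That stands as a possibility, and it is why the basis of 200 should be treated as unknown. It does not rescue the text, which presents 200 as the result of 80% power.

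It is also fair to say that 95% is not simply the power of the trial. It is a ceiling for a t-test with no deaths. Wilcoxon costs up to about 2 percentage points at efficiency 0.955, and deaths lower the power further if they leave no score. The article does not say how deaths are scored, names intention-to-treat, and excludes patients unlikely to survive to 6 months. So one can say that no mortality assumption is stated, but not that deaths were overlooked.

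The smaller points carry little weight. The 5.325, 5.5 and 5.625 are close to rounding: 14.7% rounds to 15%, and 5.5 is half of 11. Having 198 rather than 200 changes power by about 0.2 percentage points. The direction of the effect does not alter a two-sided calculation.

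A reader might infer from the shortfall of 2 patients and the missing mortality figure that 220 fails to cover the stated loss or any death. That would be so only if 200 completers were truly required. On the printed inputs about 120 are required, and 220 covers that with a wide margin.

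**Conclusion.** The sample-size statement is wrong as written. A 5.5-point difference with SD 10.65, alpha 0.05 and 80% power needs about 120 patients (about 126 for Wilcoxon), not 200, and 200 evaluable patients give about 95% power. No variant tried at alpha 0.05 and 80% power closes the gap. Which printed figure is at fault, or whether an allowance went unreported, cannot be settled from the article.

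The conclusion rests on a two-sided test, which is assumed; a one-sided test widens the gap. The power figures after deaths rest on assumed mortality and on deaths leaving no PCS. The documents do not support a claim that the trial is underpowered on its own inputs. The harm is to the reading of the result, because the chance of missing a 5.5-point effect is misreported or the SD is.

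**What to change.** Keep 220. First, the authors should state which input produced 200 and correct that figure: the SD with its source, the power, the difference, or any added allowance. They should also state whether the test is one-sided or two-sided.

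If 5.5 points and SD 10.65 stand, restate the power for 220 randomised with 10% loss and an explicit, labelled 6-month mortality assumption, taking the matching row of the second table above and giving the Wilcoxon figure alongside the t-test figure. Say whether patients who die are assumed to have no PCS. If a larger SD was the real basis, recompute the table with it.

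In the same edit, give one definition of the 5.5 points, describe the effect as an increase in line with the Hypothesis section, and note that 220 less 10% is 198.

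The cost is one reworded paragraph, with a matching line in Missing data. The recruitment target, endpoint and analysis do not change.

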### Recruitment

Patients enrolled in the study will be recruited from the population scheduled for gastrointestinal cancer surgery at the II Department of General and Gastrointestinal Surgery and Surgical Oncology of the Alimentary Tract and at Department of Surgical Oncology at First Teaching Hospital in Lublin, Poland, and the Department of General and Vascular Surgery at University Hospital in Opole, Poland.

## Methods

### Assignment of intervention

#### Enrolment procedure

All study participants will be enrolled from surgical departments by anaesthetic residents during presurgical assessment according to the inclusion and exclusion criteria (Table 1 and Fig. 1). Prior to entry, the patient, next of kin or legal representatives will need to sign the consent forms.

**Table 1 Tab1:** Eligibility criteria

Inclusion criteria	Exclusion criteria	
1. ICU patients in the acute phase of critical illness after gastrointestinal oncological surgery 2. Age ≥18 years 3. Central venous access available for continuous infusion of the study drugs 4. Admitted to the ICU during the previous 24 h with a minimum expected ICU stay of ≥5 days 5. Sequential Organ Failure Assessment (SOFA) score ≥ 2 6. Written informed consent from the patient or the patient’s legal representative	Exclusions associated with nutritional status: 1. Received parenteral nutrition within 7 days before randomisation 2. Expected to receive ≥20% of energy via supplemental EN and/or non-nutritional sources (e.g. glucose solution for drug dilution or lipids from propofol) during the first 3 nutritional treatment days 3. Inability to initiate EN prior to randomization 4. Body mass index <17 kg/m^2^ or >35 kg/m^2^ 5. Any congenital errors of amino acid metabolism Exclusions associated with comorbidities and allergies: 6. Known hypersensitivity to fish, egg, soybean proteins, peanut proteins, or to any of the active substances or excipients contained in SPN 7. Known hypersensitivity to milk protein or to any other substance contained in SPN 8. Hemophagocytic syndrome 9. Known history of HIV, hepatitis B and/or C 10. Any severe, persistent blood coagulation disorder with uncontrolled bleeding Concomitant therapy exclusions: 11. Chronic maintenance therapy with systemic glucocorticoid steroids (hydrocortisone >0.3 mg/kg/d). 12. Concomitant administration of chemotherapy 13. Administration of growth hormone and teduglutide within the previous 4 weeks	Laboratory exclusions: 14. Hypertriglyceridemia characterised by serum triglyceride levels >4 mmol/L (>350 mg/dL) 15. Treatment-refractory, clinically significant major abnormality in the serum concentration of any electrolyte (sodium, potassium, magnesium, total calcium, chloride, inorganic phosphate) 16. Acute liver failure with encephalopathy, including intoxication (e.g. paracetamol, death cap, golden chain) and/or liver enzymes (aspartate aminotransferase, alanine aminotransferase, gamma glutamyl transferase) or bilirubin exceeding 10 x upper limit normal Other exclusions: 17. Chronic liver failure (Child-Pugh scale B or C), e.g. secondary to drug or alcohol abuse 18. Participation in another interventional clinical trial within the previous 4 weeks 19. Pregnancy or lactation 20. Previous inclusion in the present study 21. Patient unlikely to survive to 6 months due to underlying illness 22. Receiving end-of-life-care

*EN* enteral nutrition, *ICU* intensive care unit, *SPN* supplemental parenteral nutrition

**Fig. 1 Fig1:**
[figure not shown]
Chart flow

#### Randomisation

Each eligible patient is allocated randomly during admission to one of the two groups: the early SPN or the late SPN group. The randomisation process is based on the order of admission to ICU, during which each eligible patient is given a consecutive number. Subsequently, a sealed envelope with a matching number is opened, which contains the name of either the intervention or the control group. The envelopes will be concealed and prepared according to the 1:1 ratio computer-generated randomisation table by a medical secretary who will not be involved in the trial.

#### Allocation concealment

Patients will be allocated to the early SPN or the late SPN group according to the given randomisation stored in the closed envelopes. The table will be stored in a designated safe by the medical secretary not involved in the study.

#### Equipment used

In order to assess thickness of the diaphragm on days 1, 3 and 5 of ICU stay, a Philips CX50 Portable Ultrasound Machine and a Philips Sparq Ultrasound Machine will be used.

### Participant data collection

Participant background data of age, sex, medical history, primary diagnosis, weight, height, body mass index and baseline PCS SF-36 will be collected.

#### Clinical testing data

Prior to enrolment, haemoglobin, platelet, Na^+^, K^+^, Ca, Cl^–^, Mg^2+^, P, triglyceride, alkaline phosphatase, aspartate aminotransferase, alanine aminotransferase, gamma glutamyl transferase and bilirubin levels, International Normalised Ratio, and activated partial thromboplastin time as well as presence of HIV, hepatitis B virus or hepatitis C virus will be assessed.Daily from days 1 to 7, haemoglobin, leukocyte, platelet, lactic acid, bicarbonate, urea, creatinine, bilirubin, alanine aminotransferase, aspartate aminotransferase, gamma glutamyl transferase, alkaline phosphatase, glucose, phosphorus, Na^+^, K^+^, Ca^2+^, Cl^–^, Mg^2+^, C-reactive protein, and procalcitonin levels as well as peripheral capillary oxygen saturation (SpO_2_), the arterial oxygen partial pressure to fractional inspired oxygen ratio (PaO_2_/FiO_2_), blood pH, partial pressure of carbon dioxide in arterial blood (PaCO_2_) and fluid balance will be measured.Daily from days 1 to 28 (or until discharge), the SOFA score will be measured.On days 1 and 7 of ICU stay, albumin and total proteins will be measured.On days 1, 3 and 5 of ICU stay, ultrasonographic assessment of the thickness of diaphragm will be performed.

#### Treatment and support in-hospital data

All performed surgeries will be laparoscopic or opened abdominal/thoracic surgery. The surgical sites will be grouped into oesophageal procedures, gastric procedures, bile duct, liver or pancreatic procedures, small bowel procedures, colonic procedures, and rectal procedures.

Postoperative surgical course will be assessed for postoperative complications according to the 7-grade Clavien–Dindo classification.

The level of organ support and pharmacotherapy required will be assessed according to duration of CRRT and mechanical ventilation, antibiotic administration, gastric antisecretory agents, prokinetic agents, catecholamines and insulin dose (per 24 h).

The name of EN or PN, the target volume, received volume, energy intake, protein intake, intolerance to EN or PN support, and the decrease or discontinuation of nutritional support will be assessed.

The use of invasive devices such as central catheters, urinary catheters, enteral route devices and endotracheal tubes, with the dates of insertion and removal, will be recorded. All those parameters, treatments and devices will be controlled until day 28 or until discontinuation, whichever occurs first.

The occurrence of hospital-acquired infections such as ventilator-associated pneumonia, bacteraemia, catheter-related infections or urinary tract infections will be recorded.

#### Follow-up data

Each patient will be followed-up until day 180. The vital status will be recorded at ICU discharge, hospital discharge and on day 28. Follow-up data will be collected by study investigators and study nurses. We plan to collect two phone numbers per patient to increase the likelihood of patient follow-up at 3 and 6 months after allocation to the study group (Fig. 2).

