### Outcomes

#### Primary endpoint

The long-term quality of life will be measured by the physical component of the 36-SF questionnaire assessed by a phone call at 3 and 6 months after admission to the ICU (License number QM047431 CT198126 OP073545 OGSR).

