### Statistical analysis

The assumption of this trial is to match the results in adherence to intention-to-treat analysis. Patient demographic data and baseline characteristics will be presented with the use of descriptive statistics. For the summary of continuous data, we plan to apply minimum and maximum values, medians, means, standard deviations and quartiles. A summary of categorical variables will be presented as distribution (with the use of percentage and numbers). We plan to analyse the primary outcome, which is the PCS SF-36, by Wilcoxon’s test and general linear regression. We expect data to be non-normally distributed.

For the secondary outcomes, we plan to use the χ^2^ test for dichotomous variables and Wilcoxon’s test as well as regression analyses for ordinal data. Time-to-event data will be compared with log rank test.

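### Intention-to-treat is promised for a score that patients who have died cannot have, and vital status is not listed at the 3- and 6-month endpoint times

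*Protocol article*

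**What the plan says.** The Statistical analysis section sets the principle: "The assumption of this trial is to match the results in adherence to intention-to-treat analysis". It then gives the primary analysis: "We plan to analyse the primary outcome, which is the PCS SF-36, by Wilcoxon’s test and general linear regression". It states no value or rank for patients who have died and does not name the set of patients analysed.

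Under Primary endpoint, the score is "assessed by a phone call at 3 and 6 months after admission to the ICU".

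The sample size Rationale rests on survivors twice. First: "The calculations were based on a PCS of 37.5 (SD 10.65) among survivors from their data". Second, the increase from 200 to 220 patients is made "assuming a 10% loss to follow-up among survivors from ICU". The Missing data section repeats the 10% allowance, this time for those who completed the trial, and does not mention death.

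Follow-up data states "Each patient will be followed-up until day 180" and plans two telephone numbers per patient for the 3- and 6-month contacts. The only times given there for recording deaths are these: "The vital status will be recorded at ICU discharge, hospital discharge and on day 28". The secondary endpoints include ICU and hospital mortality, under a 28-day heading, and no mortality at 3 or 6 months.

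**The concern.** A Wilcoxon test or regression applied to observed PCS values uses only patients who are alive and answer. Randomisation protects the comparison of everyone allocated. It does not protect a comparison of those still alive at 6 months, because survival comes after treatment and treatment may affect it. The trial lists mortality and hospital-acquired infection among its own secondary outcomes and names infection as a risk of parenteral nutrition, so a difference in survival cannot be ruled out in advance. If one arm keeps more frail patients alive, their low scores enter that arm's average. The arm with more deaths loses such patients from its average and can look better.

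The recording schedule adds to this. Without a planned check of vital status at 3 and 6 months, an unanswered call after discharge may be entered as loss to follow-up when the patient has died. An analysis plan written later can supply a rule for deaths, but it cannot supply deaths that were never systematically recorded.

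**Working it through.** **1. The passages side by side.** Intention-to-treat (Statistical analysis) requires every randomised patient to count. The outcome (Primary endpoint) exists only for the living. The planning values and the loss allowance (Rationale, Missing data) refer to survivors or completers. The vital-status times (Follow-up data) match neither endpoint time. No passage reconciles these statements.

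**2. The plan's own figure.** Inputs from the Rationale: difference 5.5, SD 10.65, significance level 0.05 (two-sided assumed), power 80%.

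n per arm = 2 × (1.960 + 0.842)² × 10.65² / 5.5² = 58.9, so 59 per arm and 118 in total.

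The stated 200 is not reproduced. That is a separate matter, but it bears on this one because 200 evaluable patients give about 95% power. With 220 randomised and 10% loss among survivors, survivor-only power by the same normal formula is:

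| Deaths by 6 months (assumed) | Patients analysed | Power |
|---|---|---|
| 10% | 178 | 93% |
| 20% | 158 | 90% |
| 30% | 139 | 86% |
| 40% | 119 | 80% |
| 50% | 99 | 73% |

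Too few survivors is therefore not the complaint. The question is which patients are compared.

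**3. Size of the bias.** The documents give no mortality by arm, so this is an assumption shown over a range. Let each patient have a standard normal robustness value with correlation ρ to PCS (SD 10.65), and let the least robust proportion m die. The mean PCS of survivors then exceeds that of all patients by

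ρ × 10.65 × φ(c)/(1 − m), where c is the m-quantile of the standard normal and φ its density.

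The factor φ(c)/(1 − m) is 0.4967 at m = 30%, 0.4237 at 25% and 0.3500 at 20%. With no true effect on PCS, the survivor difference (arm with fewer deaths minus control) is ρ × 10.65 × (factor in that arm − 0.4967):

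| ρ | 30% vs 25% | 30% vs 20% |
|---|---|---|
| 0.3 | -0.23 | -0.47 |
| 0.5 | -0.39 | -0.78 |
| 0.7 | -0.54 | -1.09 |

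The extremes are 0.23/5.5 = 4% and 1.09/5.5 = 20% of the target. For 30% vs 20% the type I error rises from 5% to 5.8%, 7.3% and 9.6% at the three correlations. With equal mortality and the same selection in both arms, the bias is zero.

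With a true gain of 5.5 points and ρ = 0.5, simulation (3,000 runs, 110 per arm, 10% loss among survivors) gives a survivor difference of about 4.7 if early supplementation has fewer deaths (20% against 30% in control). It gives about 6.3 if early supplementation has more deaths (30% against 20%).

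**4. Power when deaths are ranked lowest.** Simulation with 110 per arm, 10% loss among survivors, a 5.5-point gain, SD 10.65, and equal mortality unrelated to PCS gives about 80%, 57% and 37% at 10%, 20% and 30% deaths. Repeat runs agree to within about two percentage points.

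**The case against.** **Death handling belongs in the analysis plan.** This is the strongest point. A condensed article may leave the analysed set and the treatment of deaths to a plan that is not shown, and that absence alone would be no finding. Two things remain. The article states intention-to-treat in one section and plans on survivors in another. It also states times for recording deaths, which is a data-collection rule that no later plan can repair after the fact.

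**Recording does not simply stop at day 28.** A reader might infer that it does, or that later deaths cannot be told from losses. The text does not support this. Hospital discharge is also listed and may come later, patients are followed to day 180, and calls to two numbers will often reveal a death. The study-period figure is not shown and may list more. What stands is that the text lists no vital status at 3 or 6 months, so a late death may be misclassified.

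**The survivor restriction is not hidden.** The Rationale refers to survivors twice. It is absent only from the endpoint and analysis text.

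**A larger bias can be constructed.** If the extra survivors are assumed to score 10 to 20 points below the others, the shift becomes -0.7 to -2.5 points. Nothing in the documents supports that gap. In the model above, with 30% control mortality, even a perfect correlation gives at most about 12.5 points, and a 10-point gap needs a correlation of 0.80 to 0.86.

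**Mortality may not differ.** The Discussion reports that an earlier large trial of early versus late supplementation found no influence on mortality, and patients unlikely to survive 6 months are excluded. Both make a large difference in deaths less likely. Neither shows that mortality will be equal in this population.

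**Conclusion.** The point holds as a conflict within the document. The intention-to-treat statement does not describe what the stated primary analysis can deliver, and the listed vital-status times do not cover the primary endpoint. The survivors-only comparison follows from the score not existing after death; the gap in recording compounds it.

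The bias is conditional. It is zero with equal and similarly selective mortality. Otherwise it runs against the arm with fewer deaths, provided that frailer patients are both likelier to die and likelier to score low. About -0.2 to -1.1 points against a target of 5.5 is an illustration that rests on 30% control mortality, 5 to 10 fewer deaths per 100 in the other arm, and correlations of 0.3 to 0.7. Neither its size nor its direction in this trial can be derived from the documents. A reader might also infer that deaths will leave the trial underpowered; on the stated inputs, survivor-only power stays at 80% or more up to 40% mortality.

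**What to change.** 1. In Follow-up data, add vital status and date of death at 3 months and day 180 for every randomised patient, using the calls already planned and both telephone numbers. Report day-180 mortality by arm.
2. In Statistical analysis, state that the PCS regression and the Wilcoxon test on observed scores are analyses in survivors, not intention-to-treat.
3. Report beside them, as a companion and not a replacement, the planned Wilcoxon test on all randomised patients with deaths ranked lowest. Survivors without a score still have to be handled as missing.

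The cost is one follow-up field and one extra run of a planned test. The field has to be in place while patients are still being followed. The drawback is the companion's low power under equal mortality, down to about 37% at 30% deaths. A non-significant companion result would therefore not contradict the survivor analysis; its use is to show whether counting deaths changes the direction.
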